# A prospective non-randomized controlled trial testing the effectiveness of psychotherapeutic inpatient treatment of Post-COVID-19 syndrome - study protocol

**DOI:** 10.1186/s40359-024-01974-5

**Published:** 2024-09-16

**Keywords:** COVID-19, Post-COVID syndrome, Fatigue, Mental illness, Psychotherapy, Coping with illness

## Abstract

**Introduction:**

In addition to physical symptoms such as dyspnea, fatigue, post-exertional malaise, and pain, a subgroup of patients with Post-COVID-19 syndrome (Post-Acute Sequelae of COVID-19, PASC) suffers from mental illnesses such as anxiety, depression, and neurocognitive impairments. To date, there are no causal treatments available for PASC. While initial studies show that psychotherapy improves psychological symptoms, PASC-related fatigue, and psychosocial functioning, further research is needed to evaluate the effectiveness of psychotherapeutic treatment for PASC.

**Methods and analysis:**

This study presents a non-randomized controlled trial aimed at evaluating the effectiveness of a five-week multimodal inpatient psychosomatic treatment program for individuals experiencing PASC symptoms and comorbid mental illness. A total of 118 patients presented at the Post-COVID Center at the Universitätsklinikum Erlangen will be assigned to the intervention group receiving inpatient psychosomatic treatment or the control group receiving treatment as usual. The inclusion criteria for the intervention group are a diagnosis of PASC and at least one condition of mental distress and problems with coping with illness. The primary objective of the intervention is to reduce mental ailments, including depression and anxiety, as well as neurocognitive deficits, and to address PASC symptoms such as fatigue and pain. The core elements of the treatment are psychotherapy in individual and group settings, medical treatment, neurocognitive training, and physical therapy, adapted to the individual’s capacity and oriented towards the concept of pacing. After enrollment, participants will undergo a 6-month follow-up to assess long-term results and the sustainability of the intervention effects.

**Discussion:**

This study examines the effectiveness of inpatient psychotherapeutic treatment in PASC patients with comorbid mental illness in comparison with a control group based on treatment as usual. The results of the study can contribute to the development of evidence-based interventions to address the complex needs of patients with PASC and comorbid mental illness.

**Trial registration:**

German Clinical Trial Register (DRKS), retrospectively registered 15.02.2024 DRKSID DRKS00033562.

**Supplementary Information:**

The online version contains supplementary material available at 10.1186/s40359-024-01974-5.

## Introduction

The World Health Organization (WHO) characterizes Post-COVID-19 syndrome (Post-Acute Sequelae of COVID-19, PASC) as a condition where new or ongoing symptoms arise three months after the initial SARS-CoV-2 infection, lasting for a minimum of twelve weeks and lacking an alternative explanation [1, 2]. Among those infected with SARS-CoV-2, 6.2% experience at least one of three PASC symptom clusters, which include persistent fatigue with bodily pain or psychological problems, neurocognitive problems, or ongoing respiratory issues. Prevalence rates of PASC vary between different studies and subgroups, with the highest rates among women and those who required hospitalization for the initial SARS-CoV-2 infection [3–5]. Worldwide, physicians face considerable difficulties in treating PASC due to the absence of specific biological markers for clear diagnostic classification and the lack of causal therapies, complicating effective treatment of PASC and raising economic costs due to frequent contact with general practitioners and specialist physicians [6]. For those affected, PASC not only significantly impairs their quality of life [7], but also their ability to work. In 2022 alone, the German Pension Insurance reported 21,000 inpatient rehabilitation treatments for PASC [8] and 1,000 approved pensions for those unable to return to work due to the condition [9].

Approximately one-fifth of PASC patients also reveal mental health comorbidities such as anxiety, depression, symptoms of PTSD, and disruptions in sleep patterns [10, 11], with a prevalence of depressive and anxiety symptoms 12 months after SARS-CoV-2 infection at 23% and 22%, respectively. The prevalence of insomnia was found to be 12% [12], while other studies estimated sleep disturbances to be as high as 45% [13]. Posttraumatic symptoms after SARS-CoV-2 infection range from 6.5 to 42.8%, particularly high in those who had severe SARS-CoV-2 infection [14]. There is also accumulating evidence that preexisting psychological and psychosomatic conditions, such as symptoms of depression and anxiety, loneliness, and perceived stress, are vulnerability factors for the appearance of PASC symptoms [15]. Notably, depressive symptoms along with anxiety symptoms were found to persist for an extended period [16–18] and can significantly impact an individual’s quality of life [7].

One possible explanation for the occurrence of accompanying mental illness in PASC patients may be the difficulties in coping with illness, a concept explained by the stress-coping model [19]. The onset of a chronic illness is typically associated with psychosocial stress arising from e.g. physical limitations, the unpredictability of the disease’s progression, threats to social roles and activities, financial problems, and disruptions in self-concept and emotional well-being [20]. Effective stress management depends on evaluating stressors and having adequate coping resources, e.g. psychological stability or social support [19]. When stress exceeds these resources, the likelihood of mental illness increases [21, 22].

At the same time, psychosocial factors, in addition to biomedical factors, play an important role in maintaining and exacerbating persistent physical symptoms, defined as distressing somatic complaints lasting several months or longer. Psychosocial factors can include cognitive-perceptual and emotional mechanisms such as symptom focusing, catastrophizing interpretations, and disease-related fears or behavioral processes such as avoidance behavior, physical inactivity, and deconditioning [23]. This interplay of biomedical and psychosocial factors is also discussed for the persistence of physical symptoms in PASC [24, 25]. An initial study showed that psychological distress associated with persistent symptoms that occurred during the first year of the pandemic predicted the presence of at least one persistent symptom 6–10 months later [26]. This finding underscores the possible role of psychosocial stress in the disease course of PASC.

Initial studies have shown positive effects of psychotherapeutic interventions in PASC in outpatient and rehabilitative settings. Cognitive behavioral interventions applied in an outpatient setting lead to an improvement in fatigue symptoms and improved coping in PASC patients [27, 28]. Multimodal inpatient rehabilitation treatment with psychotherapeutic elements showed a reduction in psychological and somatic symptoms and an improvement in activity and social participation [29]. However, while psychotherapeutic interventions for PASC have been evaluated in outpatient and rehabilitation settings, results on the effectiveness of psychotherapeutic interventions established in acute care of psychosomatic treatment are lacking. When we refer to “psychosomatic treatment” in the following, we mean inpatient multimodal, focus-orientated psychotherapy for the treatment of PASC patients with mental disorders.

To address mental disorders and coping with PASC symptoms, we will use psychotherapeutic interventions which include e.g., psycho-education, coping with fear of progression, working on resources, relaxation techniques, working on emotions, and cognitive methods such as cognitive restructuring [30]. These approaches are already used as interventions for chronic illnesses, e.g. in psycho-oncological care and rehabilitation of chronic diseases, and can help patients manage their illness more effectively [31, 32]. To treat more physical symptoms of PASC, such as breathing problems and fatigue, we will supplement psychotherapeutic interventions with physiotherapy. Research on other chronic diseases, such as multiple sclerosis, has demonstrated the beneficial effects of aerobic exercises on fatigue symptoms [33, 34]. Furthermore, aerobic exercise was shown to be effective and safe as an early intervention after (severe) SARS-CoV-2 infection [35] as well as a treatment to improve PASC-related fatigue and functional capacity [29, 36, 37]. When combined with the concept of pacing - a self-management strategy that involves tailoring physical and cognitive activity to the individual’s energy levels [2]- aerobic exercise can be safely incorporated without risking post-exertional malaise (PEM), a worsening of chronic fatigue symptoms after minimal physical or mental exertion [38]. Various studies have shown that activity pacing positively impacts fatigue severity in chronic diseases [39–41]. Aerobic exercise can also improve neurocognitive functioning, which has been shown in a rehabilitation exercise program that incorporates resistance, endurance, and balance training, as well as education and pacing strategies [36]. To further alleviate the neurocognitive impairments, we will use computerized neurocognitive training, which has shown promising results in PASC patients according to initial studies. [42].

In order to appropriately tackle all these issues of PASC, an integrated multimodal approach in a psychosomatic treatment setting is ideal. In our trial, we are testing this inpatient psychosomatic PASC setting for effectiveness with a control group. Key endpoints include changes in the severity of PASC (primary outcome), as well as overall physical and mental health symptoms such as insomnia, fatigue, PEM, neurocognitive impairments, anxiety, and depression (secondary outcomes). Additional secondary outcome measures include perceived social support, distress, sense of coherence, quality of life, and coping with illness. Moreover, outcomes like healthcare utilization and treatment satisfaction are assessed.

### Objectives and hypothesis

The objective of the proposed trial is to address PASC symptoms and provide an effective treatment for PASC patients with accompanying mental illness. We aim to assess the effectiveness of a five-week inpatient treatment in the Department of Psychosomatic Medicine and Psychotherapy at Universitätsklinikum Erlangen.

### Primary hypothesis

We expect the intervention to be superior to treatment as usual (TAU) regarding a significantly lower mean of PASC symptoms measured by the Post-COVID Syndrome Scale (PCS Score) post-treatment and at 6 months follow-up.

### Secondary hypothesis

We expect the intervention to be superior to TAU in terms of reducing depression and anxiety symptoms, fatigue, sleeping problems, and perceived stress that relates to the illness as well as improving neurocognitive functions, patient competence to cope with illness, perceived social support, overall quality of life, and sense of coherence.

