### Study design

This is a prospective non-randomized controlled trial. It is a two (group: intervention and control) by three (time: pre-treatment, 5 weeks, 6 months) repeated measures factorial design. The overall study design is illustrated in Fig. 1 and Table 1. In T0 sociodemographic data, medication, and use of previous psychotherapeutic inpatient or outpatient treatments, as well as data on health behavior (e.g. smoking, alcohol consumption, etc.) of the patients will be collected. Participants in the intervention group will complete a comprehensive web-based questionnaire battery at three time points: at the time of admission to the hospital setting (T0), at the end of inpatient treatment five weeks later (T1), and 6 months after discharge from the hospital setting (T2). The control group will accomplish the questionnaire within a time frame of around 6 months after presentation at the Post-COVID Center of the Universitätsklinikum Erlangen (T0), five weeks after T0 (T1), and 6 months after T0 (T2). The questionnaires at T0, T1, and T2 will be made available web-based via a link and a password. Participants who drop out of the intervention or control group will be reported in the final results. Before participation, written informed consent must be given. A schematic overview of the trial flow is given in Fig. 1. The instruments used at each time point are displayed in Table 1.

**Table 1 Tab1:** Overview of the assessment schedule for both groups

Measures	Assessment time points		
	Baseline (T0)	5 weeks later (T1)	6-month follow-up (T2)
Sociodemographic variables	X		
Health behavior	X	X	X
Use of PASC-specific treatments		X**	X
Use of PASC-specific outpatient or inpatient psychotherapeutic treatment	X	X**	X

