**Neurocognitive testing***			
Declarative verbal memory (retrieval and recognition of VLMT)	X	X	
Cognitive processing speed and cognitive flexibility (TMT)	X	X	
Numerical short-term memory and working memory (Digit span backwards of WMS – R)	X	X	
Attention and concentration (d2 – R)	X	X	
Formal lexical and semantic verbal fluency (RWT)	X	X	

* Only for the intervention group

** Only for the control group

PCS Score, Post-COVID Score; PHQ-15, Patient Health Questionnaire-15; PHQ-9, Patient Health Questionnaire-9; GAD – 7, Generalized Anxiety Disorder Scale – 7; ISI, Insomnia Severity Index; FSS, Fatigue Severity Scale; PEM, Post-Exertional Malaise; ESSI, ENRICHD Social Support Instrument; SOC-3, Sense of Coherence Scale-3; PSS-4, Perceived Stress Scale-4; SSD-12, Somatic Symptom Disorder-12; PUK-2, Patient Competence in Coping with Cancer Questionnaire adapted for PASC symptoms; SF-36, Short Form Health Survey Questionnaire; VLMT, Verbal Learning and Memory Test; TMT, Trail Making Test; WMS-R, Wechsler Memory Scale-R; d2-R, Attention and Concentration Test; RWT, Regensburger Verbal Fluency Test

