The neuropsychological test battery will consist of the following validated assessments: the Verbal Learning Memory Test (VLMT) [63], the Digit Span Backwards from the Wechsler Memory Scale-Revised (WMS-R) [64], the Trail Making Test (TMT) Parts A and B [65], the d2 Test of Attention [66], and the Regensburger Verbal Fluency Test (RWT) [67]. The VLMT evaluates verbal memory, including delayed free recall (the retention of learned words over time) and recognition ability. The Digit Span Backwards subtest from the WMS-R measures working memory. The TMT assesses visuomotor processing speed, attention, and executive functions such as mental flexibility. The d2 Test of Attention measures selective attention and processing speed. The RWT evaluates both formal lexical (phonemic) fluency and semantic fluency, which are indicators of divergent thinking.

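### Superiority over treatment as usual is hypothesised for neurocognitive function, but only the intervention group takes the neurocognitive tests

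*Protocol article*

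**What the plan says.** The section on the secondary hypothesis is a between-group statement. It opens "We expect the intervention to be superior to TAU in terms of reducing depression and anxiety symptoms" and carries the same comparison through "perceived stress that relates to the illness as well as improving neurocognitive functions". The last paragraph of the Introduction, which presents the trial as a test against a control group, names "insomnia, fatigue, PEM, neurocognitive impairments, anxiety, and depression (secondary outcomes" among its endpoints.

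Table 1 schedules five test rows under the heading "Neurocognitive testing": VLMT, TMT, digit span backwards, d2-R and RWT. All are at T0 and T1, with nothing at T2. The heading carries the single-asterisk footnote, "Only for the intervention group". The double asterisk, "Only for the control group", is used on the treatment-use rows at T1.

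The text on the battery under the main secondary outcomes ("The neuropsychological test battery will consist of the following validated assessments") names no group. The Study design section describes control data collection only as a questionnaire ("The control group will accomplish the questionnaire within a time frame of around 6 months after presentation"), delivered by web link and password.

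**The concern.** A claim of superiority over TAU needs a value under TAU. For the neurocognitive tests the schedule provides none, and the article names no substitute such as norms or historical controls.

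The topic is not marginal to the trial. The Abstract includes neurocognitive deficits in what the intervention is meant to reduce, computerised training is one of the four treatment cornerstones, and the Strengths and limitations section counts the test battery as a strength.

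The risk is that a significant pre-post gain in the treated group is read as support for a hypothesis that was written as a comparison with TAU. The same performance tests are repeated after about five weeks, so some gain is plausible without any treatment effect.

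**Working it through.** **Step 1: hypothesis against schedule.**

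| Item | Hypothesis or outcome list | Collected in intervention group | Collected in control group |
|---|---|---|---|
| Questionnaire outcomes named in the hypothesis (depression, anxiety, fatigue, sleep, stress, coping, social support, quality of life, sense of coherence) | superior to TAU | T0, T1, T2 | T0, T1, T2 |
| Neurocognitive tests (5) | superior to TAU | T0, T1 | none |

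Tests with a control value: 0 of 5.

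The result does not hinge on which footnote the heading carries. The single asterisk means intervention group only; the double asterisk would mean control group only. Either way only one group is tested. The single-asterisk reading is the one that fits, because the same mark stands on satisfaction with treatment, also an intervention-only measure, and because controls are described as receiving questionnaires only.

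**Step 2: what can be estimated.** The primary analysis model is a mixed ANOVA with condition, time and their interaction. With one group tested, neither the condition effect nor the interaction is identified. Only the mean T0-T1 change in the intervention group remains:

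observed change = treatment effect + retest gain + natural course + regression to the mean.

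One equation cannot separate four terms. With no T2 test, nothing can be said about persistence at 6 months, even within the intervention group.

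**Step 3: how easily the remaining analysis turns significant without a treatment effect.** This illustrates the risk; the conclusion does not depend on it.

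The plan gives no sample size for the neurocognitive tests. Its own figure is for the PCS Score: 98 participants, 49 per group. That figure reproduces as a between-groups repeated-measures test with f = 0.25, three measurements and correlation 0.5: λ = f²·N·m/(1 + (m − 1)ρ) = 0.0625 × 98 × 3 / 2 = 9.19 on 1 and 96 df, power 0.851.

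Inputs for the illustration:
- n = 49 in the intervention group, from the sample size section.
- Two-sided 0.05, from the same section.
- Correlation ρ = 0.5. The section assumes this for the PCS Score; using it for performance tests is a further assumption.
- Retest gain g = 0.3 SD, range 0.2 to 0.4. Assumed; the article gives no retest figure.
- True treatment effect = 0.

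Formulas, in units of the test's SD: SD of change = √(2(1 − ρ)); noncentrality = g·√n / SD of change; power from the noncentral t with 48 df (critical value 2.011).

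At ρ = 0.5, SD of change = √(2 × 0.5) = 1 and √49 = 7, so noncentrality = 7g.

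| ρ | SD of change | g = 0.2 | g = 0.3 | g = 0.4 |
|---|---|---|---|---|
| 0.5 | 1.000 | 0.28 | 0.54 | 0.78 |
| 0.7 | 0.775 | 0.43 | 0.76 | 0.94 |
| 0.8 | 0.632 | 0.58 | 0.90 | 0.99 |

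The entries are probabilities of a significant gain for one test with no treatment effect, against a nominal 0.05.

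**The case against.** The strongest reply accepts the mismatch and disputes its weight. Five points can be made.

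- The probabilities rest on an assumed retest gain and on a correlation taken from a symptom score. That is true, and they should be read only as illustration. Varying the correlation upwards raises them, so the range at 0.5 is the lower part of what is plausible if performance tests correlate more strongly. The count of 0 of 5 needs no assumption.
- The hypothesis names no time point for secondary outcomes, so leaving out a T2 test contradicts nothing specific. This stands. The missing T2 value limits what can be concluded but is not a separate error.
- Nothing in the article says that a within-group gain will be reported as superiority over TAU. This also stands: the documented fact is that the component is untestable, and misreporting is a risk, not a stated plan.
- The Abstract states an aim of treatment and the strengths paragraph praises the breadth of measurement; neither makes an explicit between-group claim about cognition. That is fair, so edits there are clarifications. The strengths paragraph does go on to speak of evaluating the intervention's effects.
- Only one item in a long list of secondary outcomes is affected, and Table 1 discloses the restriction. Disclosure in a footnote does not make the hypothesis testable.

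None of these removes the contradiction. Nor can it be left to an analysis plan, because the gap is in the data to be collected.

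**Conclusion.** The concern holds. As written, the neurocognitive part of the secondary hypothesis cannot be tested: 0 of 5 tests have a control value, and no other comparator is named. This rests only on the article's own schedule and its description of control data collection. The uncontrolled change that can be estimated would often be significant from retest gain alone: about 54% for a 0.3 SD gain, and 28% to 78% for 0.2 to 0.4 SD, with 49 completers and correlation 0.5, the gain and the correlation being assumptions. The finding is confined to neurocognitive function. It must be corrected because a pre-specified efficacy hypothesis has no data behind it, and the correction is most credible if made before results are known.

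**What to change.** - Remove neurocognitive function from the superiority hypothesis and from the secondary outcomes of the controlled comparison in the Introduction.
- Define it as an exploratory, uncontrolled description of T0-T1 change in the intervention group, reported as estimates with confidence intervals.
- State that the change includes retest effects and natural course, that no effectiveness claim will be made, and that nothing is measured at T2.
- Add a clarifying phrase in the Abstract and in the Strengths and limitations section so that the battery is not read as part of the controlled evaluation.

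The cost is wording and the loss of one secondary efficacy claim; no extra testing is needed.

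The alternative is to give controls the same battery at T0 and T1. This would also resolve the contradiction and keep the hypothesis, but it means added testing of a group now reached only by web questionnaire, and it cannot recover baseline values for controls already past T0.

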## Methods

For reporting the outcomes of inpatient psychosomatic treatment for PASC, the SPIRIT (Standard Protocol Items: Recommendations for Interventional Trials) reporting guideline will be used [43]. In case of important protocol modification, it will be reported to the sponsor and the ethics committee, and the trial registration will be updated. Results will be published in peer-reviewed journals, conference presentations, and among self-help organizations.

